### Flowchart

Justification of no placebo online training in the control group and single-blinded design:

(A1) We consider the placebo effect of the online training as being part of the active intervention as it would be implemented in real-world practice which implies that the study will measure effectiveness rather than efficacy and that it is pragmatic rather than explanatory.

(A2) The inclusion of the placebo effect as part of the active intervention compared to usual care without placebo in the control group is further justifiable as no competing therapy exists.

(A3) Any placebo online training that we develop is likely to have some beneficial effect, due to non-specific therapeutic mechanisms like structure, hope and working alliance. Such beneficial effect in the control group will reduce the measured difference in effectiveness and would not be an accurate reflection of what can be expected in real-world practice.

(A4) Blinding of patients to the intervention itself is impossible since they are themselves actively participating in the online training.

## Study procedures

At baseline, 3-months, and 1 year all patients will undergo exercise tolerance testing, measurement of heart rate, blood pressure and resting respiratory rate, cortisol measurement in 2 cm of scalp hair, and NTproBNP measurement and they will be asked to fill out questionnaires concerning quality-of-life, psychological well-being, medical resource use, and non-health care costs. Exercise tolerance will be measured with the 6-minute-walk test (in which the distance is measured that a patient can walk within 6 minutes).

NTproBNP will be determined in a blood sample. These samples will be coded in storage. Cumulative cortisol will be measured in 2 cm of one hair taken from the scalp. Clinical follow-up will provide data required for the composite endpoint.

Quality-of-life will be evaluated with the SF36. Psychological well-being will be determined with the Hospital Anxiety Depression Scale (HADS).

Preference values with be evaluated with the EuroQol EQ-5D-5L (societal values), the SF-6D from the SF-36 answers, and the VAS rating scale (patient values). Social support will be measured with the perceived social support scale 12 (PSSS12). Medical consumption will be measured with the Tic-P.Health care costs which will be determined on the basis of medical resource use multiplied by the actual or reimbursed costs per resource. Related non-health care costs will be determined using questionnaires (Tic-P) and will consist of the time costs for undergoing procedures, time costs for self-care including the mindfulness-training, the costs for support and care, costs for complementary care, and friction costs.

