**Sample size calculation**

To demonstrate an improvement of 5% in the active intervention group vs 1% in the control group in exercise tolerance (expressed in percentage exercise tolerance compared to what can be expected given the patient’s age and sex) would require 99 patients in the control group and 198 in the active intervention group (SD10%, alpha=0.05, power=0.90, ratio experimental to controls=2). Even if only 50% of patients in the experimental group adhere to the training, we would in the as-treated analysis compare three groups of each 99 patients, which would give us a power of 0.80. To account for non-adherence and loss to follow-up a total of 330 patients will be randomized. This number of patients will be sufficient to demonstrate a smaller difference (5% vs 2%) in a repeated measurements analysis with a power of 75-90% (2 follow-up measurements, correlation between follow up measurements=0.70, correlation between baseline & follow-up=0.50).

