### Secondary study parameters/endpoints

Key secondary outcome (measured at baseline, 3 months, 1 year):

- quality-of-life (SF36), using the mental- and physical composite outcome scales

Other secondary outcomes (measured at baseline, 3 months, 1 year):

- heart rate, blood pressure, resting respiratory rate (markers of cardiac fitness)
- NTproBNP (a biomarker for heart failure)
- cumulative cortisol in 2 cm of hair taken from the scalp (cumulative measure of stress)
- composite endpoint (all-cause mortality, heart failure, arrythmia, cardiac surgery, percutaneous cardiac intervention, electrical cardioversion)
- psychological well-being (Hospital Anxiety Depression questionnaire)
- preference values (societal EuroQol EQ-5D-5L values, societal SF-6D values obtained from the SF-36, VAS rating scale [Philip Moons version])
- Social support (perceived social support scale 12 Blumenthal PSSS12)
- Medical consumption of health-care use
- health care costs
- related non-health care costs (Tic-P)

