## Recruitment and consent

*The patient information letter and informed consent form should be attached as a separate document.*

1. Potentially eligible patients will be sought by considering every patient that is scheduled for a routine outpatient visit for periodic follow-up of congenital heart disease or cardiomyopathy.
2. Four weeks prior to the patient’s routine outpatient visit, the patient will be informed by post with written information about the study. (See attached patient information letter)
3. Two weeks later the written information will be followed by a telephone call by a junior doctor (researcher / PhD student) in which oral information will be given and any questions that the patient may have about the study will be addressed. Eligibility criteria will be tested at that time. In addition, intention-to-participate will be verified. If the patient is eligible and intends to participate in the study, exercise testing and lab work will be scheduled to take place as part of the patient’s next outpatient visit 2 weeks later.
4. During the outpatient visit, the junior doctor will address any remaining questions that the patient may have about the study and obtain written informed consent. (see attached informed consent form). If the patient refuses participation at that time the baseline measurements will not be performed and the scheduled tests will be cancelled.
5. If the patient consents to be included, the junior doctor will perform the 6 minute walk test, measure heart rate, blood pressure and resting respiratory rate, take one scalp hair, guide the patient through the questionnaires (to be filled out on a computer during the outpatient visit), and guide them to the laboratory for blood work.
6. The outpatient visit will be performed as usual. The treating doctor will give lifestyle advice as usual.
7. Following the outpatient visit and baseline measurements the patient will be randomized by computer and, if randomized to the active intervention, he/she will receive an email and letter with the appropriate link to the online training. The clinical researchers on the study will not be involved in this step and will therefore be unaware of the treatment assignment.

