## Benefits and risks assessment, group relatedness

All patients will be given usual care which includes lifestyle advice. Patients in the active intervention group will, in addition, be offered an online training for the duration of 12 weeks with email messages and assignments 1-3 times per week, followed by reminder messages once every 2-4 weeks for another 40 weeks. At baseline, 3-months, and 1 year all patients will undergo 6 minute walk test and blood tests, one scalp hair will be taken, and they will be asked to fill out quality-of-life, psychological well-being, medical resource use and cost questionnaires.

There is no risk of the active intervention. We anticipate that the active intervention will improve patients’ psychological well-being and physical fitness.

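### One scalp hair per visit gives the cortisol assay about 0.1 mg of material, which may be too little unless the assay is validated for that amount

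*Protocol*

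**What the plan says.** Section 7.1.2 lists cumulative hair cortisol among the other secondary outcomes, below the key secondary outcome (SF36), and has it measured at baseline, 3 months and 1 year. It is the only outcome that the protocol labels a measure of stress.

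The outcome list and the Summary's endpoint paragraph give a length of 2 cm and no number of hairs. The first paragraph of section 7.3 does the same: "cortisol measurement in 2 cm of scalp hair".

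Four places give the number, and each time it is one:

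- Section 7.3, second paragraph: "Cumulative cortisol will be measured in 2 cm of one hair taken from the scalp".
- Section 10.2, step 5, the instruction to the junior doctor at the baseline visit: "take one scalp hair".
- Section 10.4, on burden at all three time points: "one scalp hair will be taken".
- The Summary's paragraph on burden and risks, in the same words as section 10.4.

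The protocol names no assay, minimum hair weight, expected concentration or quantification limit.

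**The concern.** The number of hairs is a stated sampling rule, repeated in the operational step and in both burden statements, so it cannot be put down to a slip in one place. Staff who follow it will send the laboratory one 2 cm hair per patient per visit, and nothing in the protocol shows that this is enough to assay.

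If it is not enough, many values will lie below quantification or be dominated by assay error in both arms. A lack of difference between the arms would then say little about stress. Up to 330 × 3 = 990 samples are collected under this rule. The pre-training sample cannot be taken again once the training has begun, so a shortfall found late could not be repaired for the baseline.

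**Working it through.** The protocol gives no figure on this point to reproduce. Only the length of 2 cm comes from it. The other inputs are assumptions, shown as ranges:

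- hair diameter d: 50 to 100 micrometres
- density: 1.3 g/cm³
- cortisol content: 5 to 50 pg/mg
- smallest quantifiable amount per extract: 5 to 50 pg, with about 1 pg as a more sensitive case

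**Step 1: mass of one segment.** Mass = π × (d/2)² × length × density. For d = 70 micrometres = 0.007 cm: π × 0.0035² × 2 × 1.3 = 0.000100 g = 0.10 mg. For 50 micrometres the result is 0.051 mg, and for 100 micrometres 0.204 mg.

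**Step 2: cortisol in the whole sample.** Amount = mass × content.

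| Diameter | Mass | 5 pg/mg | 10 pg/mg | 25 pg/mg | 50 pg/mg |
|---|---|---|---|---|---|
| 50 µm | 0.051 mg | 0.26 pg | 0.51 pg | 1.3 pg | 2.6 pg |
| 70 µm | 0.100 mg | 0.50 pg | 1.0 pg | 2.5 pg | 5.0 pg |
| 100 µm | 0.204 mg | 1.0 pg | 2.0 pg | 5.1 pg | 10.2 pg |

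The range is about 0.3 to 10 pg. Widening the density to 1.1–1.35 g/cm³ and the content to 1–100 pg/mg gives about 0.04 to 21 pg.

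**Step 3: comparison with a limit.** At 5 pg, three of the twelve cells reach the limit; at 10 pg, one does; at 50 pg, none. At 1 pg, nine do. The cells show how the answer depends on the assumptions and are not proportions of patients. Even with the wider inputs, nothing reaches 25 pg.

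**Step 4: content needed for a 0.10 mg hair.** Content needed = limit / mass. A limit of 1 pg needs 1 / 0.10 = 10 pg/mg; 5 pg needs 50 pg/mg; 10 pg needs 100 pg/mg. Splitting the sample for a duplicate halves the mass to 0.05 mg and doubles each of these, so a 1 pg limit then needs 20 pg/mg.

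**Step 5: mass needed.** Mass needed = limit / content. Over limits of 5 to 50 pg and contents of 5 to 50 pg/mg, this runs from 5 / 50 = 0.1 mg to 50 / 5 = 10 mg, or about 1 to 100 hairs at 70 micrometres. For a 1 pg limit it is 1 / 50 = 0.02 mg to 1 / 5 = 0.2 mg. The minimum weight therefore has to come from the assay.

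**The case against.** The strongest objection is that the protocol contains neither a cortisol content nor an assay limit. The geometry is sound, but any statement about quantification rests on assumptions, and with a limit near 1 pg one hair could be adequate over much of the range. This stands. A reader might infer that the outcome cannot be measured as written, or that one hair is short by about two orders of magnitude. The protocol does not support either: the second figure corresponds to a need of 10 mg, which is only the worst corner of the assumed ranges.

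A reader might also see a contradiction between 2 cm of hair in the outcome definition and one hair in the procedure. There is none. One gives a length, the other adds a number, and one hair can supply 2 cm.

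The importance should not be overstated either. Section 7.1.1 names three routes to better fitness: breathing exercises, a healthier lifestyle, and less chronic anxiety and stress. The HADS also covers anxiety. The introduction lists heart rate, blood pressure and respiration rate among the responses to stress modification, and the trial measures all three, though under the label of cardiac fitness.

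Finally, assay choice, minimum weight and the handling of values below quantification can properly sit in a laboratory manual or analysis plan that is not shown. Their absence is no error. That does not remove the point: the protocol itself fixes the number of hairs, and a manual that asked for more would conflict with four places in it.

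**Conclusion.** The point holds as a conditional concern about feasibility. The protocol commits each visit to one 2 cm hair, about 0.1 mg (0.05 to 0.20 mg), holding about 0.3 to 10 pg of cortisol under the assumed content. The outcome may be unmeasurable or very imprecise unless the assay is validated for about 0.1 mg, and even a sensitive assay would have almost no material for a replicate or repeat run.

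The mass rests on ordinary geometry and an assumed diameter and density. The verdict on quantification rests on an assumed content and limit, and changes with the assay. The effect is confined to one of the other secondary outcomes. The primary outcome (6-minute walk test) and the sample size are untouched.

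**What to change.** Before baseline sampling, confirm with the laboratory the smallest hair mass for which the chosen assay is validated. In the Summary's burden paragraph, section 7.3, section 10.2 step 5 and section 10.4, replace the single hair by a small lock cut close to the scalp. State a minimum weight for the 2 cm segment, taken from that validated minimum, with no fixed figure such as 10 mg written in beforehand. Describe the same sample in the patient information letter, which is not shown here.

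The cost is wording in the protocol and the letter, and a slightly larger cut at visits that already take place. A few patients who would have given one hair may decline a lock. No extra visits or patients are needed.

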## Withdrawal of individual subjects

Subjects can leave the study at any time for any reason if they wish to do so without any consequences. The investigator can decide to withdraw a subject from the study for urgent medical reasons. If a patient decides to withdraw, the investigator will ask the patient consent for including the data collected thus far in the analysis.

A potential problem would arise if a large group of patients randomized to the active intervention are non-adherent to the active intervention. Nevertheless, non-adherence is considered part of what can be expected in the future when such an intervention is implemented in everyday practice and thus effectiveness rather than efficacy is measured.

### Specific criteria for withdrawal (if applicable)

None

## Replacement of individual subjects after withdrawal

None

## Follow-up of subjects withdrawn from treatment

None

## Premature termination of the study

Since we are investigating a complementary no-risk lifestyle intervention there will be no reason for premature termination of the study.

# SAFETY REPORTING

## Section 10 WMO event

In accordance to section 10, subsection 1, of the WMO, the investigator will inform the subjects and the reviewing accredited METC if anything occurs, on the basis of which it appears that the disadvantages of participation may be significantly greater than was foreseen in the research proposal. The study will be suspended pending further review by the accredited METC, except insofar as suspension would jeopardise the subjects’ health. The investigator will take care that all subjects are kept informed.

## Adverse and serious adverse events

Adverse events are defined as any undesirable experience occurring to a subject during the study, whether or not considered related to the experimental treatment]. All adverse events reported spontaneously by the subject or observed by the investiga­tor or his staff will be recorded.

A serious adverse event is any untoward medical occurrence or effect that at any dose:

- results in death;
- is life threatening (at the time of the event);
- requires hospitalisation or prolongation of existing inpatients’ hospitalisation;
- results in persistent or significant disability or incapacity;
- is a congenital anomaly or birth defect;
- is a new event of the trial likely to affect the safety of the subjects, such as an unexpected outcome of an adverse reaction, lack of efficacy of an IMP used for the treatment of a life threatening disease, major safety finding from a newly completed animal study, etc.

All SAEs will be reported through the web portal *ToetsingOnline* to the accredited METC that approved the protocol, within 15 days after the sponsor has first knowledge of the serious adverse reactions..

SAEs that result in death or are life threatening should be reported expedited. The expedited reporting will occur not later than 7 days after the responsible investigator has first knowledge of the adverse reaction. This is for a preliminary report with another 8 days for completion of the report.

### Suspected unexpected serious adverse reactions (SUSAR)

Not applicable because the intervention is not an investigational medicinal product

### Annual safety report

Not applicable because the intervention is not an investigational medicinal product

## Follow-up of adverse events

All adverse events will be followed until they have abated, or until a stable situation has been reached. Depending on the event, follow up may require additional tests or medical procedures as indicated, and/or referral to the general physician or a medical specialist.

## Data Safety Monitoring Board (DSMB)

The general DSMB of the Erasmus MC / LUMC will be asked to oversee this study. The advice(s) of the DSMB will be notified upon receipt by the sponsor to the METC that approved the protocol. With this notification a statement will be included indicating whether the advice will be followed.

# STATISTICAL ANALYSIS

## Descriptive statistics

Descriptive statistics will be calculated to describe the study population and to determine if any chance differences exist between the groups. Formal tests for differences will not be performed since we trust that the randomization procedure will be properly performed. Missing values will be imputed with a multiple imputation approach. The results will be tabulated.

## Intention-to-treat and as-treated analysis

An intention-to-treat analysis will be performed to address whether offering mindfulness training is effective and cost-effective. Patients that are non-adherent to the offered training (cross-overs to usual care) will be analyzed as part of the active intervention group. Similarly, control patients who seek interventions on their own will be analyzed in the usual care group to which they were allocated.

An as-treated analysis will be performed to address whether mindfulness training is beneficial if actually performed and the treatment effect depending on the degree of adherence. The usual care group will consist of the control group. In the active intervention group, adherence to the intervention is monitored (see ‘’Intervention’’) and completion of sufficient number of training modules will be the criterion to determine which patients in the active intervention arm are included in the ‘’on-treatment’’ group. The ‘’on-treatment’’ group will consist of those patients who complete 50% or more of the exercises in the first 12 weeks. Patients who start the mindfulness training but complete less than 50% of the assignments in the first 12 weeks will be considered non-adherent and analyzed separately as the “partially treated’’ group. We will also evaluate outcome as function of the proportion of completed exercises as a continuous variable adjusting for potential confouders in a multivariable model. Finally, we will use the method developed by Robins and Tsiatis that corrects for non-compliance in randomized trials using rank preserving structural failure time models [25-26].

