# STUDY DESIGN

Pragmatic randomized controlled single-blind trial.

Duration: 12 months

Setting: outpatient clinic of an academic hospital

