## Univariable analysis

Short-term results (3 months) and mid-term results (1 year) will be calculated. Differences in mean improvements between the groups will be calculated for all outcome measures expressed on a continuous scale. Analysis with repeated measurement methods (mixed models) will be performed to account for multiple measurements performed during follow-up and for missing values.

Survival analysis will be performed with a failure being an event as defined according to the composite endpoint.

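### As-treated groups set by training done in the first 12 weeks would bias a survival comparison of the composite towards benefit, if they are applied to it with time from randomisation

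*Protocol*

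**What the plan says.** Protocol 9.2 (Intention-to-treat and as-treated analysis) sets three groups for the as-treated analysis:

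- The on-treatment group "will consist of those patients who complete 50% or more of the exercises in the first 12 weeks".
- Patients who start but "complete less than 50% of the assignments in the first 12 weeks will be considered non-adherent and analyzed separately" form the partially treated group.
- For the reference, "The usual care group will consist of the control group", with no condition on surviving or being followed to any time point.

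The same section adds a model with the proportion of exercises completed as a continuous variable, and a method that "corrects for non-compliance in randomized trials using rank preserving structural failure time models". It does not say which outcomes the as-treated analysis covers.

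Protocol 9.3 (Univariable analysis) states: "Survival analysis will be performed with a failure being an event as defined according to the composite endpoint". It also says "Short-term results (3 months) and mid-term results (1 year) will be calculated". It gives no time origin, landmark, delayed entry or time-varying exposure. Section 7.1.2 lists the outcome as "composite endpoint (all-cause mortality, heart failure, arrythmia, cardiac surgery, percutaneous cardiac intervention, electrical cardioversion"). Section 3 gives "Duration: 12 months". Under section 10.2, the link to the training is sent only after randomisation.

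**The concern.** Adherence status is decided by what a patient does after randomisation, in a period when composite events can already occur. A patient who dies before completing half the exercises can never be on-treatment. One who stops training after heart failure or surgery is counted as partially treated. Controls face no such filter and carry every early event. If time runs from randomisation, the on-treatment group is credited with early time in which some of its would-be members' events have been moved elsewhere.

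The direction is predictable: apparent benefit in completers and apparent harm in non-completers, even if training does nothing. The adjustment for baseline factors in 9.4 does not correct it, because the fault lies in the time axis. The proportion-completed model has the same weakness if it is used for the composite, since an early event can itself lower the proportion.

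The as-treated result will be read. The primary objective in section 2 concerns the effect of training, with offering it as the secondary objective, and 9.2 uses the as-treated analysis to ask about training that was actually performed.

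**Working it through.** **The plan's own figures.** The protocol gives no event rate or power for the composite. Its figures concern the walk test (section 4, sample size calculation): difference 5 − 1 = 4 points, SD 10, two-sided alpha 0.05 (sidedness is not stated, but two-sided reproduces the figure), power 0.90, ratio 2:1.

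- Controls: (1 + 1/2) × (1.960 + 1.282)² × 10²/4² = 98.5, so 99, with 198 active. This matches.
- 99 against 99: power 0.804, against the stated 0.80.
- 297/0.90 = 330. This matches, and 2:1 gives 220 and 110.

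These figures stand and do not bear on the composite.

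**Inputs for the composite.**

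- From the protocol: 12-week classification window, 12 months of follow-up (12/52 = 23% of it lies in the window), 50% adherence as the planning case in section 4, and material sent every 3 days (5.1). If the material is spread evenly, half of a 12-week course takes about 6 weeks.
- Assumed: constant hazard; 1-year event risk of 5% to 30%; half-completion reached evenly over weeks 6 to 12 (mean week 9); and a share q of events before that mark that end training. The documents give neither the risk nor q.

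**Approximation under no effect.** At low risk, about 9/52 of the events of would-be adherers fall before their half-completion mark, and a share q of these leaves the group. So

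rate ratio, on-treatment vs control ≈ 1 − q × 9/52

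- q = 0: 1.00
- q = 0.25: 0.96
- q = 0.5: 0.91
- q = 1: 0.83

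**Simulation under no effect** (220 vs 110 patients, 1,500 replicates per scenario; ranges are over 1-year risks of 5% to 30%). The last column takes in both timings of the half-completion mark.

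| q | Rate ratio vs control, mark at weeks 6–12 | Rate ratio vs control, mark only at week 12 | False benefit rate (nominal one-sided 0.025) |
|---|---|---|---|
| 0 | 1.00–1.02 | 0.97–1.01 | 0.023–0.030 |
| 0.25 | 0.94–0.97 | 0.94–0.95 | 0.030–0.053 |
| 0.5 | 0.90–0.92 | 0.86–0.88 | 0.037–0.075 |
| 1 | 0.80–0.82 | 0.75–0.77 | 0.049–0.197 |

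The rest of the active arm shows the mirror image. With the mark at weeks 6–12, its rate ratio against control is 1.04–1.06, 1.08–1.10 and 1.18–1.20 for q = 0.25, 0.5 and 1. That group also includes patients who never start, so it is wider than the protocol's partially treated group.

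**If everyone keeps exactly to schedule**, the mark is at week 6. The ratio is then 1 − 6/52 = 0.88 at q = 1 and 1 − 3/52 = 0.94 at q = 0.5.

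**At 3 months.** If the composite were also compared by adherence at 3 months, the classification and outcome windows would nearly coincide. With T = 13 weeks, 1 − q × 9/13 gives 0.83, 0.65 and 0.31 for q = 0.25, 0.5 and 1.

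**Against sampling error.** Take 110 per group and an assumed 15% risk, so about 16.5 events each. The standard error of the log rate ratio is √(2/16.5) = 0.35, and a 95% interval around 1 runs from about 0.5 to 2. The bias at ratios of 0.95 and 0.91 is |ln 0.95|/0.35 = 0.15 and |ln 0.91|/0.35 = 0.27 standard errors. At 0.82 it is 0.57.

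**With a 12-week landmark**, the null rate ratio on-treatment vs control was 0.97–1.03 in every scenario.

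**The case against.** The strongest objection is that the faulted analysis is inferred. Section 9.2 does not mention the composite, and the survival sentence in 9.3 mentions no as-treated groups. Where the protocol ties the as-treated analysis to an outcome, it is the walk test: the Summary places it directly after the primary outcome, and section 4 gives its power for exercise tolerance. This stands, so the point has to be conditional. A reader might infer that the protocol prescribes an immortal-time comparison of events. It does not say so; its wording allows one and does nothing to prevent it.

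A reader might also take the named failure-time method as part of the problem. It is not. It compares the arms as randomised and does not use the 50% rule, so it avoids this bias. Because the composite is the only failure-time outcome in the protocol, naming the method does suggest that adherence analyses of events are intended. It does not show that the completion groups are to be used for them.

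The size can also be contested. Arrhythmia or cardioversion need not stop an online course, and at q = 0 the bias vanishes. Planned operations and percutaneous interventions are excluded and age is capped at 65, which plausibly reduces early procedures and deaths. At middle values of q the bias is well under one standard error. All of this stands.

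Finally, the time origin and a landmark could be left to an analysis plan that is not shown. This is only partly an answer. The protocol itself fixes the classification window and an unconditioned comparator, and that pairing is unsuitable for a time-to-event outcome.

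**Conclusion.** The point holds in conditional form. Applied to the composite with time from randomisation, the grouping rule in 9.2 gives a comparison biased towards benefit. Under no effect, 50% adherence and half-completion between weeks 6 and 12, the 1-year rate ratio against control is roughly 0.95, 0.91 or 0.82 for q = 0.25, 0.5 or 1, and 1.0 for q = 0. If the mark is reached only at week 12, the lower end is about 0.75. These values rest on assumed event risks and an assumed q.

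The documents do not support the reading that the trial's conclusions on clinical events are compromised. The intention-to-treat analysis, the rank preserving analysis and the walk-test sample size are untouched. At middle values of q, random error in a trial of this size outweighs the bias. The case for acting is that the direction is known in advance and the remedy is cheap.

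**What to change.** Add to 9.2 or 9.3 that any as-treated or proportion-completed analysis of the composite uses a 12-week landmark: adherence is fixed at week 12, all groups including controls are restricted to patients event-free and in follow-up then, and the clock starts there. State that intention-to-treat from randomisation is the main result for this endpoint, and that the rank preserving model gives the adherence-corrected estimate.

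The cost is one or two sentences. Events in the first 12 weeks, and any 3-month as-treated result for the composite, are lost from this supportive analysis. A landmark does not remove selection by who chooses to adhere. That selection was not part of the simulation, and the text should acknowledge it as a remaining limitation.
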